# Justification of Methodology

The study trial shall involve 100 patients with type 2 diabetes as determined above. The trial shall last 22 weeks (10 weeks treatment time and 12 weeks follow-up) which we realized enough time to determine whether a clinically significant effect will be produced. We employed a randomized controlled design to determine if any change is significantly different from a control group not receiving the acceptance and commitment therapy. Control group allow us to determine if variability in diabetes control within individuals has overshadowed the impact of potential confounders. Examples of factors that could influence variability within individuals include age, sex, educational level, diabetes duration and medical treatment.

**3.1.2 Setting:**

The Endocrinology department of Labbafinejad hospital is an ideal center from which to adequately supervise and conduct the study. Study participants will be patients with type 2 diabetes recruited from Endocrinology department through specialist referral to researchers and talks led by the trial investigators. Participants will be fully informed of the treatment they may receive and must give informed consent before enrolment.

**3.1.3 TIME LINE**

The subjects will be directly involved in the study for twelve weeks. We intend on recruiting for the trial immediately upon approval of the trial by Ethics Committee of the Research Institute for Endocrine Sciences, Shahid Beheshti University of Medical Sciences.

Recruitment should take three to six weeks and if possible be complete early February. We will commence with treatment after recruitment of eligible participants, which is projected to end of February. The trial itself will be completed for 6 months.

1. **ETHICS**

We have passed this study through the Ethics Committee of the Research Institute for Endocrine Sciences, Shahid Beheshti University of Medical Sciences for ethics approval. Informed consent will be obtained from all enrolled subjects. All authors declare that they have no conflict of interest.

1. **FUNDING**

Part of the financial support for this project is provided by Tarbiat Modares University.

**APPENDIX A**

**Brief COPE**

These items deal with ways you've been coping with the stress in your life since you found out you were going to have to have this operation.  There are many ways to try to deal with problems.  These items ask what you've been doing to cope with this one.  Obviously, different people deal with things in different ways, but I'm interested in how you've tried to deal with it.  Each item says something about a particular way of coping.  I want to know to what extent you've been doing what the item says.  How much or how frequently.  Don't answer on the basis of whether it seems to be working or not—just whether or not you're doing it.  Use these response choices.  Try to rate each item separately in your mind from the others.  Make your answers as true FOR YOU as you can.

 1 = I haven't been doing this at all
 2 = I've been doing this a little bit
 3 = I've been doing this a medium amount
 4 = I've been doing this a lot

| 1.  I've been turning to work or other activities to take my mind off things.  2.  I've been concentrating my efforts on doing something about the situation I'm in.  3.  I've been saying to myself "this isn't real.".  4.  I've been using alcohol or other drugs to make myself feel better.  5.  I've been getting emotional support from others.  6.  I've been giving up trying to deal with it.  7.  I've been taking action to try to make the situation better.  8.  I've been refusing to believe that it has happened.  9.  I've been saying things to let my unpleasant feelings escape.  10.  I’ve been getting help and advice from other people.  11.  I've been using alcohol or other drugs to help me get through it.  12.  I've been trying to see it in a different light, to make it seem more positive.  13.  I’ve been criticizing myself.  14.  I've been trying to come up with a strategy about what to do.  15.  I've been getting comfort and understanding from someone.  16.  I've been giving up the attempt to cope.  17.  I've been looking for something good in what is happening.  18.  I've been making jokes about it.  19.  I've been doing something to think about it less, such as going to movies,   watching TV, reading, daydreaming, sleeping, or shopping.  20.  I've been accepting the reality of the fact that it has happened.  21.  I've been expressing my negative feelings.  22.  I've been trying to find comfort in my religion or spiritual beliefs.  23.  I’ve been trying to get advice or help from other people about what to do.  24.  I've been learning to live with it.  25.  I've been thinking hard about what steps to take.  26.  I’ve been blaming myself for things that happened.  27.  I've been praying or meditating.  28.  I've been making fun of the situation. |  |
| --- | --- |

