***Purpose and benefits of the study***

This study has two purpose:1- To examine whether acceptance and commitment therapy works for participants with a diagnosis of type 2 diabetes and whether it provides clinically significant improvement in HbA1c reduction and improvement in self-management compared with the control group. 2- To assess the moderating role of coping styles in the relationship between acceptance and commitment therapy and self-management of patients with type 2 diabetes.

Perhaps the main contribution the study could give is that it opens up for other psychological modator and mediators in the effect of acceptance and commitment therapy on development of diabetes control. Therefore, this study may become important. this will be important information as many Mindfulness-Oriented Therapist already engaged in acceptance and commitment therapy

1. **PROPOSED STUDY**

This randomised controlled trial will evaluate the efficacy of acceptance and commitment therapy to effectively control diabetes. This will be an intervention trial using treatments and one-day educational workshop. The study sample will be randomised into two arms: treatment and control. The study population will consist of 100 patients with type 2 diabetes.

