## Study Overview

### 2.1.1 Methodology

Setting and Participants: The setting for this study will be the Endocrine Department of Labbafinejad Hospital in Tehran. The study will involve patients with type 2 diabetes. The study population will be male and female, in the age groups from 40 to 60. Sampling and Recruitment: Recruitment for the study will be facilitated by Labbafinejad Hospital. Participants will be introduced to researchers by the endocrinologist from the endocrine department. Interested parties will be encouraged to contact the psychologist directly and provide their name, phone number and preferred time of contact. Interested participants will be given an Information Kit, which will include: a sample consent form, a Backgrounder explaining the purpose of the study and contact list and phone numbers of the psychologist and researchers involved in the study.

Interested participants will be encouraged to ask questions to their Endocrinologist and directly to the Psychologist. The participants will be introduced to researchers by the endocrinologist from the endocrine department to participate in a 1-day educational workshop for self-management of diabetes,and all participants will be received a one-day workshop about diabetes control and will be encouraged to complete several questionnaires on socio-demographic characteristics, Summary of Diabetes Self-Care Activities (SDACA), Beck Depression Inventory, Acceptance and Action Diabetes Questionnaire and Brief COPE Questionnaire. then weight and height will be measured and blood samples will be obtained. Eligible participants will be randomly assigned to either the control or treatment groups (using the random number table), and will be booked for further appointment times.

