**2.1.2 Components of the Treatment**

The group acceptance and commitment therapy (ACT) will be delivered during 10, 2-hour sessions and each session of study is one week.

Across problems in living, ACT is a treatment that is difficult to deliver with integrity. The application of ACT to diabetes is no different, and contains specific challenges as well. The goal of the treatment is to compassionately assist patients in dealing with any thoughts, feelings, worries, anxieties, or fears they may have related to their disease and its maintenance in order to help them live their life in a valued direction related to their diabetes. A key first step in this holistic approach to diabetes self-management is to provide adequate information about how to care for one’s diabetes in order to address the specific motivational and acceptance pieces laid out in the treatment. Thus, the first half of the treatment provides specific information regarding the management of diabetes and the second half of the treatment addresses motivational and acceptance issues related to engaging in self-management behaviors. The treatment is divided into 5 main modules:

Module I: Education and Information

Module II: Food, Diabetes, and Your Health

Module III: Exercise and Diabetes

Module IV: Coping and Stress Management

Module V: Acceptance and Action

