**Exclusion criteria**

1) Have other kinds of diabetes (type 1 and Gestational diabetes)

2) If they had been hospitalized

3) Lack of satisfaction could not collaborate or continue in the study.

4) Any current serious disorders determined to be clinically significant to the study.

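### The Brief COPE printed in Appendix A asks about coping with an operation, not with diabetes; used as printed, it would leave the coping-style moderator tied to a wrong or undefined stressor

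*Protocol*

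**What the plan says.** The protocol's second purpose is "To assess the moderating role of coping styles in the relationship between acceptance and commitment therapy and self-management of patients with type 2 diabetes". Section 2.1.1 lists the instruments completed at the start, ending with the "Acceptance and Action Diabetes Questionnaire and Brief COPE Questionnaire". It places questionnaire assessments before therapy, after the last session and at three months. The end of section 2.1.2 names the Brief COPE again in the follow-up package. No other coping questionnaire is listed.

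Appendix A gives the only form of the Brief COPE in the protocol. Its instruction concerns stress "since you found out you were going to have to have this operation" and then ties the ratings to that stressor: "These items ask what you've been doing to cope with this one". The 28 items follow.

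Section 2.1.6 plans three separate two-way analyses of covariance for the moderating role of coping styles. Their outcomes are glycated haemoglobin, self-care activities and acceptance.

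**The concern.** The Brief COPE instruction has two jobs: it names the stressor and it sets the period to recall. In Appendix A both are tied to a coming operation. A patient whose condition is type 2 diabetes and who expects no surgery has no such event to think of.

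The second of the study's two purposes is at stake. The Introduction presents the role of moderators as the gap in the literature that the study addresses, and coping style is the one moderator chosen. If patients settle on different stressors, the scores do not measure one common thing, and a treatment-by-coping interaction, present or absent, is hard to interpret.

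Timing matters too. Section 2.1.6 does not say which administration supplies the moderator. If it is the pre-treatment score, as is usual for a moderator, a faulty baseline cannot be repeated later in the therapy arm, because the fourth module of the treatment works directly on avoidance coping.

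**Working it through.** The point depends on no sample size, power or error rate, and the plan states no figure to reproduce. The check sets the relevant parts of the protocol side by side.

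1. **Population.** Section 2.1.1: "The study will involve patients with type 2 diabetes". The age range is 40 to 60. No inclusion criterion in section 2.1.4 concerns surgery, and one exclusion reads "If they had been hospitalized". That criterion gives no period and does not mention operations, so it is only supporting evidence. The main fact is that nobody is enrolled because of an operation.

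2. **Intervention.** Section 2.1.2: "The group acceptance and commitment therapy (ACT) will be delivered during 10, 2-hour sessions". Controls receive the one-day workshop and a waiting list. Neither arm involves surgery.

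3. **Instruction.** Appendix A names an operation as the event since which coping is rated ("since you found out you were going to have to have this operation"). This is a complete sentence in the current text.

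4. **Items.** None of the 28 items mentions diabetes or an operation. Where they point to a stressor they use a pronoun or a general word, as in item 20: "I've been accepting the reality of the fact that it has happened". The items therefore do not correct the instruction.

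5. **Adaptation.** No section says that the instruction was changed for this trial, and none states the version or language used.

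6. **Use in the analysis.** Coping style enters the three two-way analyses of covariance. The three one-way analyses of covariance and the repeated-measures analysis in section 2.1.6 compare the arms after adjustment for pre-test scores on the outcomes. Coping is not among their terms.

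Steps 1 to 4 show that the printed instruction contradicts the protocol's own population. Step 5 shows that the protocol does not resolve this. Step 6 confines the consequence to the second purpose.

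**Can the effect be sized?** One could try the classical attenuation formula, observed slope = reliability × true slope. With an assumed reliability of 0.5 to 0.8, the slope would lose 1 − 0.8 = 20% to 1 − 0.5 = 50%. This is not a valid size for the defect:

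- The protocol gives no reliability. The percentages only restate the assumption.
- A correctly worded form also has reliability below 1. The cost of the wrong instruction would be 1 − (reliability with the wrong wording ÷ reliability with the right wording). With assumed values of 0.7 and 0.8 that is 1 − 0.7/0.8 = 12.5%. Across pairs in the assumed range it runs from 0 (both equal) to 1 − 0.5/0.8 = 37.5%. Nothing in the document selects a value.
- The formula is for a continuous moderator with random error. A two-way analysis of covariance suggests that coping style is a grouping factor, where the problem would be misclassification.
- Rating the wrong stressor is a validity problem. The error may be systematic, so a shift toward zero cannot be assumed.

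**The case against.** The strongest reply is that the protocol never says the Appendix A text will be handed out word for word. Sections 2.1.1 and 2.1.2 only name the questionnaire. The appendix is in English, the trial recruits in Tehran, and an adapted version may well have been intended. This stands in part. A reader might infer that the moderator will certainly be measured against the wrong stressor; the document supports this only on condition that the form is used as printed. It does not remove the point, because Appendix A is the only form given and an unrecorded spoken correction could differ between patients or visits.

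A second reply is that context would rescue the answers. Patients are referred by an endocrinologist and complete the form in connection with a diabetes workshop, alongside two diabetes questionnaires, and the items read naturally for diabetes. Many could well take diabetes as the stressor. This is a fair limit on how much harm to expect. It also means that any particular pattern of answers, such as rating a past operation or skipping items, is conjecture. It is no reason to leave the stressor to be guessed.

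A third reply is that this is a template phrase left in an appendix, with no bearing on the randomised comparison. The part about the randomised comparison is correct and limits the severity. But the phrase sits in the instrument that supplies the moderator, and questionnaire wording is not something a statistical analysis plan would normally set right.

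**Conclusion.** The point holds in a limited form. Appendix A prints an instruction that does not fit the trial's population, the items name no stressor, and the protocol records no adaptation. Used as printed, the form would leave the coping-style moderator, and with it the second purpose and the three two-way analyses of covariance, tied to a wrong or undefined stressor. This is an inconsistency within the document and should be fixed.

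Two stronger readings are not supported. A reader might infer that a known share of the interaction is lost, or that it is pulled toward zero; neither the size nor the direction of any bias can be derived from the document. A reader might also infer that the trial's main result is in doubt. It is not: the comparisons of therapy with control on HbA1c, self-care and acceptance do not use the Brief COPE.

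The conclusion rests on one assumption, that patients would receive the Appendix A instruction or a faithful translation of it.

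**What to change.** Before the first baseline assessment, replace the phrase about the operation in Appendix A with one that refers to the patient's diabetes, for example the stress in your life related to having diabetes. The 28 items can stay as they are. State the version and language given to patients, put that same diabetes wording into it, and use it unchanged at pre-test, post-test and follow-up.

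The cost is one sentence in the questionnaire and a notice to the ethics committee. It adds no visits, no participants and no burden on patients. The change has to come before baseline data are collected, because the pre-treatment coping score cannot be obtained again once therapy has begun.

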**Appendix B**

[figure not shown]

